#### Power.

Our preliminary study, with a sample of 46 participants, found significant within-subjects improvement across all outcomes and significant between-group differences in measures of EF and PS, with medium to large effect sizes for all findings [60]. Thus, with a recruitment goal of 90 participants in the current study, we expect to have significantly more power than our previous study. The power analyses for the current study were conducted using the pwr [98] and longpower [99,100] packages in R [101]. To power the proposed study at the 0.8 level (3 group RCT) to detect a medium between-group effect size (α = 0.05, two-tailed) with 20% attrition (a reasonable estimate based on our previous study [60] and consistent with dropout rates in psychotherapy RCTs [102]) would require a total sample of 195 or 65 per group. While this is obviously not feasible in a 3-year study (2.5 years actual recruitment, including database preparation, cleaning, and publication time at the end of the study) supported by a small grant mechanism, our proposed sample is twice that of our prior study. Also, in a previous study looking at CCN activation using the emotional go/no go task, significant activation was found in a number of different areas of the CCN with only 24 participants [103]. With a proposed sample size of 90, we are confident about detecting medium to large effect sizes across our proposed cognitive and neural activation variables of interest.

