## METHODS

### Study Design Features and Rationale

Ninety young adults exhibiting mild to moderate depressive symptoms will be randomized in an 8-week computerized cognitive training (CCT) trial delivered via smartphone application. Mobile-based CCT was chosen as it is particularly relevant for young adults, with 92% of those aged 1829 owning a smartphone [81]. Mobile CCT is also consistent with the goal of personalizing medicine as it is easily accessible, inexpensive, noninvasive, and scaled to the skill level of each individual. Neuropsychological and clinical assessments will take place at Queens College, City University of New York, and fMRI will be conducted at The Graduate Center’s MRI facility, the Advanced Science Research Center. Participants will be randomized to one of three conditions: processing speed/executive functioning (PS/EF) CCT, verbal ability CCT (active control), or waitlist control (undergo assessment and imaging procedures and will be not be given access to the training program until 8-week completion). The randomization sequences will be balanced in blocks of random size to prevent researchers from guessing what the next participant’s condition assignment might be. In order to reduce expectancy bias, the informed consent signed by all participants prior to participation will not indicate which condition is the intervention, the active control, or the waitlist control. Instead, the consent will indicate that the participant will be assigned to one of three groups, two which target different aspects of brain functioning and the third which will begin cognitive training after 8 weeks.

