### Hypotheses

The primary aim of the study is to determine whether PS/EF-focused CCT is superior to, and leads to faster improvement than, verbal ability-focused CCT and waitlist control. Hypothesis 1: there will be greater improvement in mood, cognition, and everyday functioning in participants randomized to CCT (both PS/EF and verbal) compared to waitlist control. Hypothesis 2: there will be greater improvement in EF and PS outcomes in participants randomized to PS/EF CCT compared to verbal CCT and waitlist control. Hypothesis 3: there will be faster improvement in mood, cognition, and everyday functioning in participants randomized to PS/EF CCT compared to verbal CCT and waitlist control.

The secondary aim of the study is to determine whether PS/EF-focused CCT leads to greater change in CCN activation (task-based fMRI) and connectivity (resting state fMRI) than verbal ability-focused CCT and waitlist control. Hypothesis 1: there will be a greater increase in CCN activation and connectivity among participants randomized to PS/EF CCT and verbal CCT compared to waitlist control. Hypothesis 2: there will be a greater increase in CCN activation and connectivity among participants randomized to PS/EF CCT compared to verbal CCT. Hypothesis 3: clinical improvements will be positively associated with an increase in CCN activity and connectivity.

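### The Power paragraph claims confidence in medium neural effects with 90 participants, although it calculates that 195 are needed and its one fMRI precedent does not bear on a between-arm difference in change

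*Protocol article*

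**What the plan says.** All of the sample-size reasoning is in the Power paragraph of the protocol article.

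- **Formal calculation.** It is for 80% power in a three-group trial, "to detect a medium between-group effect size (α = 0.05, two-tailed) with 20% attrition". The result is that this "would require a total sample of 195 or 65 per group". The authors call that infeasible under their grant.
- **Support for 90 instead.** They cite the preliminary study of 46 participants, the doubling of its sample, and, for imaging, an earlier emotional go/no-go study in which "significant activation was found in a number of different areas of the CCN with only 24 participants".
- **Conclusion.** With 90, "we are confident about detecting medium to large effect sizes across our proposed cognitive and neural activation variables of interest".

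The Hypotheses section frames the imaging aim as a comparison of change between arms, for example that "there will be a greater increase in CCN activation and connectivity among participants randomized to PS/EF CCT compared to verbal CCT". The Aim 2 section tests activation (the primary fMRI outcome) with an independent-sample t-test on contrast images. It tests the connectivity index (secondary) with a regressed change model: week 8 adjusted for week 0, arms dummy-coded, waitlist as reference.

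**The concern.** Two statements in one paragraph do not fit together. If 195 participants are needed for 80% power at a medium between-group effect, then 90 cannot justify confidence about medium effects in between-group comparisons. The cited imaging study does not close the gap. Finding activation during a task answers whether the task engages the network. Aim 2 asks whether eight weeks of training changes that engagement more in one arm than in another. The precedent, as reported, supplies no estimate of such a difference.

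The number 24 can also reassure by coincidence, because 30 per arm less 20% attrition is 24 per arm. The two numbers refer to different questions.

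The trial's title is about mechanism of action. If readers take the stated confidence at face value, a null PS/EF versus verbal imaging result could be read as evidence against the mechanism, when the comparison had less than an even chance of detecting a medium effect.

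**Working it through.** **Inputs from the protocol.** Total 90; three arms; 20% attrition; two-sided 0.05; target power 0.80; medium between-group effect, with no number given.

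**Assumptions.** Equal allocation (implied by 195 = 3 × 65). Medium means f = 0.25 for the three-group test or d = 0.5 for a two-arm comparison. One summary measure per test, with no correction across voxels, regions or comparisons. d is standardised on the scale that is analysed.

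**Step 1: reproduce the 195.** One-way ANOVA, 3 groups, f = 0.25, alpha 0.05, power 0.80 gives 157.2 in total, or 52.4 per group. Allowing for attrition, 157.2 / 0.8 = 196.5; with 52 per group, 52 / 0.8 = 65, so 3 × 65 = 195. Power at 156 completers is 0.797. The stated figure is therefore reproduced to within rounding by f = 0.25. A two-arm t-test at d = 0.5 would give 64 / 0.8 = 80 per group, or 240 in total, which does not match.

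**Step 2: arm sizes at 90.** 90 / 3 = 30 per arm; 30 × 0.8 = 24 completers per arm, or 72 in total.

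**Step 3: three-group power at the same medium effect.** Noncentral F with λ = f² × N:
- N = 72: λ = 0.0625 × 72 = 4.5, power 0.443.
- N = 90: λ = 0.0625 × 90 = 5.625, power 0.540.

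**Step 4: pairwise power.** Noncentral t with noncentrality d × √(n/2) and 2n − 2 degrees of freedom:

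| Effect | 24 per arm | 30 per arm |
|---|---|---|
| d = 0.5 | 0.396 | 0.478 |
| d = 0.8 | 0.774 | 0.861 |
| d detectable with 80% power | 0.826 | 0.736 |

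Pooling both training arms against waitlist, the most favourable reading of the first imaging hypothesis, gives 0.505 (48 v 24) to 0.599 (60 v 30) at d = 0.5. That is still well short of 0.80.

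**Step 5: effect of adjusting for week 0 (connectivity only).** With pre-post correlation ρ, the detectable difference in raw standard deviation units is the Step 4 value times √(1 − ρ²). At 24 per arm, for assumed ρ of 0.3, 0.5 and 0.7:
- 0.826 × 0.954 = 0.79
- 0.826 × 0.866 = 0.72
- 0.826 × 0.714 = 0.59

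**Step 6: what the preliminary study adds.** It compared two groups, so 46 / 2 = 23 per group on average, against 30 per arm here, or 24 after attrition. The doubled total therefore adds little per arm. The Introduction describes that study's results for cognition, mood and everyday function, and presents the neural mechanism as what the new trial adds.

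**The case against.** The best defence is that the paragraph is candid. It says the fully powered size is out of reach, the imaging aim is secondary, the Abstract speaks of exploring network functioning, and the Conclusion says the results will help size a larger trial. Nothing in the document says that a null imaging result would count against the mechanism. This stands, and it makes the point one of wording. It does not rescue the closing sentence, which still claims confidence about medium effects.

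A second defence is that baseline adjustment raises power. That is right for the connectivity index, as Step 5 shows. The primary fMRI outcome, however, is described with an independent-sample t-test and no baseline covariate.

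Three stronger readings are tempting, and the documents do not support them:

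- **That the cited study was a within-group test.** This is only an inference from the sentence. The article gives no design, group structure, threshold or effect size. Had it compared 12 with 12, and had 50% to 80% power, the implied d of 0.84 to 1.20 would have 81% to 98% power at 24 per arm.
- **That the same effect has about 53% power between arms.** This requires the earlier study to have been a one-sample test with exactly 80% power (d of about 0.60). If its power was anywhere from 50% to 95%, the figure runs from 29% to 74% at 24 per arm, or 36% to 83% at 30. It also carries over to Aim 2 an effect that, as reported, says nothing about a difference in change.
- **That this study is the only justification for 90.** The preliminary study and the doubled sample are cited too. It is only the sole imaging-specific support.

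**Conclusion.** The point holds as an inconsistency between the stated confidence and the paragraph's own calculation, together with a precedent that does not address the comparison being made. At the document's medium effect, 90 participants give about 40% to 48% pairwise power and 44% to 54% three-group power; the lower figures apply after the stated attrition. A pairwise effect of about 0.83 (24 per arm) or 0.74 (30 per arm) is needed for 80%. The claim about large effects is much closer to being supported: d = 0.8 has 77% to 86% power. So the word medium is what the design does not support.

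These figures rest on equal allocation, d = 0.5 and f = 0.25 as the meaning of medium, two-sided 0.05 and a single summary measure. Correction for multiple imaging tests would lower power; adjustment for week 0 would raise it in raw units. No power figure derived from the 24-participant study is needed for this conclusion.

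**What to change.** 1. Keep the 24-participant sentence only as evidence that the emotional go/no-go task elicits CCN activation, not as support for sample size.
2. Remove medium from the neural part of the closing sentence and state the detectable effect, for example: *With 24 to 30 scanned participants per arm, the study has 80% power for a pairwise standardised difference of about 0.83 to 0.74 on the analysis scale, before any multiple-comparison correction. For connectivity adjusted for week 0, the detectable raw-scale difference is smaller, depending on the pre-post correlation.*
3. State that PS/EF versus verbal fMRI differences will be reported as estimates with confidence intervals, so that a non-significant result is not taken as evidence against the mechanism.

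The cost is a few sentences in the Power and Aim 2 text and a less favourable claim. No participants, scans or visits are added.

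### The Power section says a medium effect needs 195 participants, then claims confidence in medium effects with 90; power there is about 0.40 to 0.54 without baseline adjustment

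*Protocol article*

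**What the plan says.** All the statements at issue stand in one paragraph of the protocol article, Statistical Analysis and Sample Size, under Power.

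- The target: power of 0.8 in the three-arm design "to detect a medium between-group effect size (α = 0.05, two-tailed"). One participant in five is assumed lost, a rate the authors take from their preliminary study and from psychotherapy trials.
- The requirement: this "would require a total sample of 195 or 65 per group".
- The concession: "While this is obviously not feasible in a 3-year study" on a small grant.
- Two arguments offered in place of a calculation for 90. The first is about the total: "our proposed sample is twice that of our prior study". The second cites an earlier imaging study, where "significant activation was found in a number of different areas of the CCN with only 24 participants".
- The conclusion: "With a proposed sample size of 90, we are confident about detecting medium to large effect sizes", said of both the cognitive and the imaging outcomes.

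The section gives no power and no detectable effect size for 90 participants. It does not put a number on medium, and it does not say which test the 195 belongs to; it names two R packages, pwr and longpower.

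**The concern.** A design that needs 195 participants for 80% power at a given effect cannot have that power with 90 on the same assumptions. The closing sentence therefore credits the trial with a sensitivity that the same paragraph has just said it lacks, and no calculation comes between the two.

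The primary aim (Hypotheses) is superiority of PS/EF training over verbal training and waitlist. If readers believe a medium difference was within reach, they may take a non-significant PS/EF versus verbal result as evidence that the two are alike. The Conclusion also says the results will be used to set the sample size of a larger trial. Estimates that reach significance in a low-power comparison tend to be too large, and that error would carry forward.

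**Working it through.** **Inputs from the article.** Power 0.80; α = 0.05 two-tailed; three groups; 20% attrition; 195 total (65 per group) for a medium effect; 90 planned.

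**Assumptions.** Medium is f = 0.25 for a three-group test or d = 0.5 for two groups. Allocation is equal, so 90/3 = 30 per arm, and 30 × 0.8 = 24 completers.

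**1. The plan's own figure.** One-way ANOVA, k = 3, noncentrality λ = 3n·f², df = 2 and 3(n − 1).
- Solving for 80% power at f = 0.25 gives n = 52.4 per group.
- With n = 52: λ = 156 × 0.0625 = 9.75 and power is 0.797. Then 52/0.8 = 65 per group and 3 × 65 = 195, as stated.
- Alternative: a two-sample t-test at d = 0.5 needs 63.8, so 64 per group. Three groups make 192 before attrition, close to 195. With attrition, 64/0.8 = 80 per group, which does not match.

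Since the text says attrition is included, the three-group test is the likely basis. A longpower calculation was not tried, so this is an inference.

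**2. Power at 90 for a medium effect.** Pairwise: noncentral t, δ = d·√(n/2), df = 2n − 2. With n = 24, δ = 0.5 × √12 = 1.73; with n = 30, δ = 0.5 × √15 = 1.94. Three-group: λ = 72 × 0.0625 = 4.5 or 90 × 0.0625 = 5.625.

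| Comparison | 24 per arm | 30 per arm (no attrition) |
|---|---|---|
| Pairwise, d = 0.5 | 0.40 | 0.48 |
| Three-group, f = 0.25 | 0.44 | 0.54 |
| Both CCT arms pooled vs waitlist, d = 0.5 (48 vs 24; 60 vs 30) | 0.51 | 0.60 |
| Pairwise, d = 0.8 | 0.77 | 0.86 |
| Three-group, f = 0.4 | 0.85 | 0.93 |

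**3. Detectable pairwise effect at 80% power, unadjusted.** d = 0.83 (24 per arm) or 0.74 (30 per arm).

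**4. With baseline adjustment.** At baseline–outcome correlation r, the detectable d is multiplied by √(1 − r²). The article gives no r, so a range is shown.

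| Assumed r | √(1 − r²) | Detectable d, 24 per arm | Detectable d, 30 per arm | Power at d = 0.5, 24 / 30 per arm |
|---|---|---|---|---|
| 0.5 | 0.866 | 0.72 | 0.64 | 0.50 / 0.59 |
| 0.7 | 0.714 | 0.59 | 0.53 | 0.66 / 0.76 |
| 0.8 | 0.600 | 0.50 | 0.44 | 0.81 / 0.89 |

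**5. The two supporting arguments.** The total has indeed nearly doubled: 90/46 = 1.96. But those 90 are spread over three arms, while the preliminary study compared two types of training (Introduction), and a between-arm test depends on the numbers per arm. The 24-participant study is described only as showing activation, with no comparison of randomized arms. Neither is a power calculation for a between-arm difference.

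None of these figures adjusts α for the three primary outcomes (HDRS, SDS, TMT-4) or for several contrasts; any adjustment would lower power.

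**The case against.** The best defence is that the shortfall is disclosed. The section gives the 195, says it cannot be reached, and the Conclusion presents the trial as informing a more powerful one. That stands as candour about the 195, but it does not cover the closing sentence, which takes the disclosure back.

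Second, an unadjusted t-test on completers understates the planned analysis. Aim 1 uses multilevel models with maximum likelihood, non-adherent participants stay in, and the connectivity analysis adjusts for the pre-score. Participants with partial follow-up contribute, so the effective number lies between 24 and 30 per arm. This stands, and it is why both columns and a range of r are shown. At r = 0.8 a medium effect is detectable even with 24 per arm, so it would be wrong to infer that no analysis could reach one. But the article neither states a correlation nor uses this gain to justify 90, and the t-test on the task-fMRI contrasts is described without baseline adjustment.

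Third, a reader might go further than the document allows in three ways:
- That 195 can only be a three-group F-test figure. Medium is not quantified and two packages are cited, so this is not established.
- That the correct requirement is 240 (3 × 80). This depends on choosing a pairwise test at d = 0.5; f = 0.25 across three arms is a different effect definition, and Hypothesis 1 of each aim sets both CCT arms against waitlist, which could be tested pooled.
- That the doubling statement is false. It is true of the totals, and an even split of the 46 is not stated.

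**Conclusion.** The point holds as a contradiction within the Power section. On the article's own requirement, 90 is less than half of the 195 needed for a medium effect. With medium taken as d = 0.5 or f = 0.25, equal allocation and no baseline adjustment, power runs from 0.40 (pairwise, 20% attrition) to 0.54 (three-group, no attrition), and from 0.51 to 0.60 for the pooled CCT contrast, against a target of 0.80. The large end of the claim is roughly sound, with pairwise power of 0.77 to 0.86 at d = 0.8. The fault lies in the word medium.

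The conclusion would soften only if the baseline–outcome correlation were high: near 0.8 with 24 per arm, or somewhat above 0.7 with 30. The article offers no evidence on this. Nothing in it says that a null result will be read as equivalence; that is a risk created by the wording, not a stated plan.

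**What to change.** Amend the Power section:

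1. Remove medium from the closing claim.
2. State, for 90 randomized, the effect detectable at 80% power and the power for a medium effect, with the attrition, test and correlation assumed. On the assumptions above: without baseline adjustment, detectable pairwise d of 0.83 with 24 per arm or 0.74 with 30, and power of 0.40 to 0.48 at d = 0.5. Any adjusted figure should name its correlation and source.
3. Have the authors state which test and which numerical effect size the 195 is based on.
4. Do not rest the claim on the doubled total or on the 24-participant activation study.
5. Commit to reporting between-arm estimates with 95% confidence intervals, and to not reading non-significance as equivalence.

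This changes text only; enrolment, endpoints and conduct are untouched. The cost is a less favourable stated sensitivity.

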## RESULTS

The NIMH grant for this protocol was received in April 2019 and study recruitment began in October 2019. We expect to finish recruitment by April 2022 and to begin data analysis once recruitment has been completed.

## ETHICS APPROVAL

This study was approved by the Queens College Institutional Review Board (IRB) in November 2018. All participants will be required to have the capacity to provide informed consent and sign the IRB-approved informed consent form. Local IRB and state regulations for consent will be followed. Participant confidentiality is maintained according to HIPAA law for potential and enrolled participants before, during, and after the trial. The cognitive testing results and the fMRI findings will not be released to the participants.

## CONCLUSION

This study is innovative in at least four distinct ways. Firstly, it investigates the mechanism of action of CCT using task-based and resting state fMRI. To our knowledge, no study has demonstrated activation of the brain in adults with depression using CCT. Targeting the CCN with novel interventions that aim to improve its functional connectivity has the potential to significantly contribute to the treatment of depression. Identifying the neural networks associated with improvements in mood following CCT will allow for the development of more precise and effective interventions. This is critical given that a large number of individuals do not or only partially benefit from antidepressant and/or psychological treatment. Secondly, it includes both active and waitlist control conditions, which will help to control for threats to validity. Thirdly, it utilizes a smartphone-based CCT intervention, which can be completed virtually anywhere creating fewer disruptions in the participants’ life. Compared to existing treatments, it is easily accessible, inexpensive, noninvasive, and scales in skill level for each individual. Our study, therefore, is consistent with the goal of personalized medicine. Finally, this study includes an assessment of everyday function thereby assessing both near and far transfer. This is crucial as most CCT studies do not evaluate whether improvements on cognitive measures occur alongside or result in improvements in everyday functioning and quality of life [104–108]. Such assessments are necessary to evaluate claims that CCT only “teaches to the test” (i.e., CCT games are similar to outcome measures) and does not improve daily functioning.

The results will also help inform the design of a more powerful randomized controlled trial in many ways: determine sample size for a larger trial, identify domains and exercises most likely to improve, learn how subjects engage, identify gender effects, evaluate long-term benefits, and understand brain networks affected.

## Figures and Tables

**Table 1. T1:** Inclusion/Exclusion Criteria.

**Inclusion Criteria**
1. Males and females ages 18–29 (inclusive) at the time of informed consent.
2. Current diagnosis of MDD/persistent depressive disorder or HDRS ≥ 12.
3. Daily access to smartphone or tablet with internet connection for the study duration.
4. Willing and able to complete fMRI, mood, and neuropsychological testing.
5. IQ ≥ 85.

